### Endpoint variables

Exclusively breastfeeding is defined as a child has only breastmilk and no other liquids or solid foods until 6 months of age. Any form of breastfeeding is defined as the child has breastmilk and other liquids or solid foods until 6 months of age. Infant feeding practices are assessed using a questionnaire of food items given to the baby in the last week or 24 h preceding the inquiry [30]. The age of child at the time of stopping breastfeeding is obtained by interviewing the mother. Infant death or hospitalization for any cause occurring within the study duration is identified by interviewing the mother. Non-routine or sick-clinic visits as reported by the mother. Infant weight and length are measured by the research assistants at study visits.

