### Sample size, power, and detectable differences

We expect an exclusive breastfeeding rate of 8% at age 6 months in the usual care group [17]. We want to detect a difference of 15% between the intervention and usual care groups (i.e., 23% vs 8%). The traditional fixed sample size computations using WinPepi give a sample size of 182 for a two-sided test. Using inflation factor 1.01 for two planned analyses of O’Brien-Fleming boundaries at the 0.05 significance level and 80% power, we compute the maximum sample size of 182 × 1.01 = 184. The sample size is inflated by 33% to 275, to account for loss to follow-up (30%) and infants who test HIV positive (3%) who are included in the analysis ignoring infant HIV status and repeat the analysis excluding HIV-infected infants. The study is not powered for the co-primary endpoint (i.e., any form of breastfeeding rate at 6 months of age) and secondary endpoints. The co-primary and secondary endpoint analyses are considered exploratory and may only be supportive of the primary analysis of exclusive breastfeeding endpoint. No adjustment to the significance level for testing of multiple co-primary endpoints is made since all the co-primary endpoint analyses are considered exploratory.

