### Statistical methods

The participant is the unit of reporting. The interim analysis includes the first 138 mother-infant pairs enrolled (half of the total enrolment). Table 2 provides a summary of methods of analysis for each endpoint. An independent data analyst performs data analysis during trial monitoring. The data analyst writes a statistical code that includes the population used in a table or figure that is explicitly set at the start of a block of code that computes the output; at the start of any code, a set of comments give references to inputs and outputs. The Stata software package is used for analysis.

**Table 2 Tab2:** Endpoints, hypothesis, and methods of analysis

Endpoint measure	Hypothesis	Method of analysis
Primary 1: exclusive breastfeeding at 6 months of child age	Text messaging and motivational interviewing lead to higher rates of exclusive breastfeeding than usual care	▪ Standard proportions test ▪ Binomial regression
Primary 2: any form of breastfeeding at 6 months of child age	Text messaging and motivational interviewing lead to higher rates of any form of breastfeeding than usual care	▪ Standard proportions test ▪ Binomial regression
Exploratory analysis of primary endpoint: time to stopping breastfeeding	Text messaging and motivational interviewing lead to a higher median time to stopping breastfeeding than usual care	▪ Kaplan–Meier survival analysis ▪ Cox proportional-hazards regression model
Secondary 1: number of all-cause infant hospitalization and death as a composite endpoint Time to first all-cause death or hospitalization	Text messaging and motivational interviewing lead to a reduction in the number of all-cause hospitalizations or all-cause deaths than usual care	▪ Mean cumulative function ▪ Poisson random-effects model ▪ Kaplan–Meier survival analysis ▪ Cox proportional-hazards model
Secondary 2: infant growth	Text messaging and motivational interviewing lead to improved infant growth than usual care	▪ Mixed linear regression models

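### The second co-primary endpoint, any form of breastfeeding, is worded as mixed feeding, so its group difference is reduced by the whole gain in exclusive breastfeeding and can change sign

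*Protocol article*

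**What the plan says.** The protocol article, Endpoint variables, defines the two co-primary endpoints in consecutive sentences. The first: "Exclusively breastfeeding is defined as a child has only breastmilk and no other liquids or solid foods until 6 months of age". The second: "Any form of breastfeeding is defined as the child has breastmilk and other liquids or solid foods until" 6 months of age. No other section says that an exclusively breastfed infant also counts towards the second endpoint.

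Table 2 (Statistical methods) lists the second endpoint as Primary 2, with the hypothesis "Text messaging and motivational interviewing lead to higher rates of any form of breastfeeding than usual care". The hypothesis for Primary 1 is parallel: "Text messaging and motivational interviewing lead to higher rates of exclusive breastfeeding than usual care".

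Three other places bear on the meaning:

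- The section on text messaging and motivational interviewing says a pair has reached the co-primary outcomes once the mother gives up breastfeeding altogether.
- Time to event endpoints, under the exploratory analyses of the primary endpoints, sets a Cox model for stopping breastfeeding beside the binomial regression to see whether the associations agree.
- Sample size, power, and detectable differences says the study is not powered for the second endpoint, calls its analysis exploratory, and allows it at most a supporting role.

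**The concern.** The two definitions are joined to breastmilk by *only* in one case and *and* in the other. As written, they describe groups that cannot overlap: infants fed breastmilk alone, and infants fed breastmilk plus something else. The name *any form* promises the union of the two.

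The weekly messages urge mothers to breastfeed exclusively. A mother who moves from mixed to exclusive feeding is a success on Primary 1 and, under the written definition, a failure on Primary 2. The comparison with the Cox model suffers too. An exclusively breastfed infant has no event in the analysis of stopping, but is a failure in a binomial model of Primary 2. The two analyses could then disagree because of the definition alone.

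An independent analyst writes the code. Following the sentence gives the wrong variable, and following the presumed intent departs from the published definition. At stake are the Primary 2 proportions and relative risk, their review by the DSMB at the interim analysis, and their use as support for the primary result.

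**Working it through.** **Inputs from the protocol article.** Exclusive breastfeeding at 6 months under usual care: "We expect an exclusive breastfeeding rate of 8% at age 6 months in the usual care group". Target: "We want to detect a difference of 15% between the intervention and usual care groups (i.e., 23% vs 8"%). Two-sided 0.05 level, 80% power, 1:1 allocation.

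**The plan's own figure.** The two-proportion formula with pooled variance and no continuity correction has mean proportion (0.08 + 0.23)/2 = 0.155:

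n per group = [1.96 × √(2 × 0.155 × 0.845) + 0.842 × √(0.08 × 0.92 + 0.23 × 0.77)]² / 0.15² = 90.2, rounded up to 91, or 182 in total.

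This matches the stated 182. Then 182 × 1.01 = 183.8, rounded to 184, and 184/(1 − 0.33) = 274.6, rounded to 275. All three figures reproduce, and they depend on exclusive breastfeeding only.

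**Effect of the written definition.** Every breastfed infant is fed either exclusively or mixed. Let A be the proportion receiving any breastmilk and E the proportion exclusively breastfed, with subscript 1 for intervention and 0 for usual care. The written endpoint is L = A − E, so

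L₁ − L₀ = (A₁ − A₀) − (E₁ − E₀) = D − (0.23 − 0.08) = D − 0.15.

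An inclusive definition gives D itself. The gap of 15 points does not depend on the usual-care level A₀.

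**Range.** The article gives neither A₀ nor D. With A₀ = 50% as an assumption:

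| D (points) | As written, usual care vs intervention | Difference | Relative risk | Inclusive, usual care vs intervention | Relative risk |
|---|---|---|---|---|---|
| 0 | 42% vs 27% | −15 | 0.64 | 50% vs 50% | 1.00 |
| +5 | 42% vs 32% | −10 | 0.76 | 50% vs 55% | 1.10 |
| +10 | 42% vs 37% | −5 | 0.88 | 50% vs 60% | 1.20 |
| +15 | 42% vs 42% | 0 | 1.00 | 50% vs 65% | 1.30 |
| +20 | 42% vs 47% | +5 | 1.12 | 50% vs 70% | 1.40 |
| +25 | 42% vs 52% | +10 | 1.24 | 50% vs 75% | 1.50 |

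If A₀ is varied from 30% to 70%, the relative risks change but the column of differences does not.

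**Could the artefact look significant?** Take the least favourable row, D = 0, with 96 per group (275 × 0.70 / 2 = 96.25, that is, after the planned 30% loss). The mean proportion is 0.345, and |z| = 0.15/√(2 × 0.345 × 0.655/96) = 2.19. With A₀ at 40% it is 2.42, and at 60% it is 2.09. These values apply to D = 0 only.

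**The case against.** The best reply is that the intent can be recovered. The label says *any form*, the intervention section refers to complete cessation, and time to stopping breastfeeding is listed as an exploratory analysis of the primary endpoint. All of these point to an inclusive endpoint and a drafting slip, so miscoding is possible rather than certain. This stands, and it lowers the severity. It does not remove the error, because the only operative definition says something else.

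A second reply is that little rests on the endpoint. It is unpowered and exploratory. The final boundary of 1.9776, the interim boundary of 2.7967 and the sample size all concern exclusive breastfeeding, and no stopping rule uses the second endpoint. This also stands.

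Two stronger readings are tempting, and the documents support neither:

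- A reader might infer that a successful intervention must lower Primary 2. It need not. The trial also hopes that fewer mothers stop altogether. If all breastfeeding rises by more than exclusive breastfeeding does, the endpoint rises even as written. The 15-point apparent harm requires D = 0, which is contrary to the trial's own hypothesis.
- A reader might say that the objectives and Table 2 treat exclusive breastfeeding as a subset of any breastfeeding. They list two parallel endpoints and state no nesting. Two non-overlapping categories can both rise if fewer mothers stop, so the paired hypotheses alone do not prove a contradiction. The case rests on the name, the cessation framing and the consistency check.

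**Conclusion.** The definition is wrong as written and should be fixed. Taken literally, Primary 2 measures mixed feeding and leaves out exclusively breastfed infants, and nothing else in the article repairs it.

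The result that always holds is a downward bias in the group difference equal to the full gain in exclusive breastfeeding, 15 points at the design values. A true gain in all breastfeeding of between 0 and 15 points would show as a loss. A gain of exactly 15 would show as no effect, and a larger one would be understated by 15 points. Which case applies depends on D, which the documents do not give. The 50% usual-care level is an illustration and does not affect the size of the bias. If the observed gain in exclusive breastfeeding differs from 15 points, the bias differs by the same amount.

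The confirmatory test, the interim boundary and the sample size are unaffected, so this is not a defect that blocks the trial. It matters because the endpoint is labelled Primary 2, is reviewed by the DSMB, and is offered as support for the primary result. An endpoint from which the primary effect has been subtracted is poorly suited to that role.

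**What to change.** In Endpoint variables, reword the second definition so that the child receives breastmilk, *with or without* other liquids or solid foods. Keep the plan's existing time frame; this correction should not be used to change it. Exclusive breastfeeding then becomes a subset of any breastfeeding, and the binomial analysis of Primary 2 addresses the same distinction, breastfed or not, as the analysis of time to stopping. If mixed feeding is of interest in itself, report it as a separate descriptive category.

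Derive the variable from the existing food-item questionnaire, and settle the rule before the interim analysis. If any interim tabulation already exists, record which definition it used.

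The cost is one sentence in the protocol and the analysis plan and one derivation rule in the code. No new data are needed, and neither the sample size nor the boundaries change.

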### Safety events

Safety events are collected from the time the participant consents to trial participation until the participant is discharged from the trial or at the trial conclusion. Potential social unintended consequences of safety events include relationship conflicts with partners due to study participation; reduced child monitoring due to exaggerated perception of the benefits of breastfeeding (assess infant immunization history as proxy), psychological stress, or guilt due to non-compliance with exclusive breastfeeding; and inadvertent disclosure of participant’s HIV status.

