### Exploratory efficacy analyses of secondary endpoints

#### Time to event endpoints

Time to first all-cause death or hospitalization is analysed using Kaplan–Meier survival curves and Cox proportional-hazards model. Time from birth to occurrence of first hospitalization or death is used as time at risk for the survival analysis.

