#### Count outcomes

A Poisson random-effects model is used to compare counts of all-cause infant hospitalization, death, and non-routine sick clinic visits between the study groups, allowing for a lack of statistical independence resulting from the observation of multiple events in some infants. Results are adjusted for calendar time to account for infant health progression, leading to a decreasing incidence of events among infants over time.

The number of all-cause infant hospitalization, death, and non-routine or sick clinic visits (composite endpoint) is compared between the study groups using the mean cumulative function. The intensity rate is reported.

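### The Count outcomes section pools mother-reported sick-clinic visits with hospitalization and death, beyond the Table 2 endpoint, so less care-seeking alone could make the composite favour the intervention

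*Protocol article*

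**What the plan says.** The protocol article describes the infant-health endpoint in two ways.

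- **Hospitalization and death only.** Table 2 names the secondary endpoint as "number of all-cause infant hospitalization and death as a composite endpoint" and expects the intervention to "lead to a reduction in the number of all-cause hospitalizations or all-cause deaths than usual care". The Objectives and hypotheses section names the same two events. The survival analysis of the secondary endpoint also keeps to them: "Time to first all-cause death or hospitalization is analysed using Kaplan–Meier survival curves and Cox proportional-hazards model".
- **Hospitalization, death and clinic visits.** The Count outcomes section says: "The number of all-cause infant hospitalization, death, and non-routine or sick clinic visits (composite endpoint) is compared between the study groups", by the mean cumulative function. The Poisson random-effects model in that section is to "compare counts of all-cause infant hospitalization, death, and non-routine sick clinic visits between the study groups".

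Three other statements bear on how a fall in clinic visits would be read. Endpoint variables gives their source: "Non-routine or sick-clinic visits as reported by the mother". Blinding says that participants know their group. Safety events lists, among possible social consequences of the trial, "reduced child monitoring due to exaggerated perception of the benefits of breastfeeding (assess infant immunization history as proxy".

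**The concern.** A clinic visit records two things at once: that the infant was ill, and that the mother sought care. Hospitalization and death depend much less on the second. In the Count outcomes composite, each visit not made lowers the count by one, exactly as a prevented hospitalization or death would.

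The protocol itself raises the possibility that mothers who overrate the protection from breastfeeding watch their infants less closely. Only the intervention group receives weekly encouragement to breastfeed by text message, so any such effect would fall mainly on that group. If it led to fewer visits for illness, the composite would move in the intervention's favour with illness unchanged. The stated proxy, immunization history, reflects routine attendance. It neither shows care-seeking in illness nor corrects the composite.

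At stake is how one exploratory result is read. The Discussion says that the findings may inform decisions on whether the interventions affect child health and survival, so a lower event count could be taken for better health.

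**Working it through.** **1. Figures in the plan.** The plan gives no rate for clinic visits, hospitalizations or deaths, so it has no figure of its own to reproduce on this point. From Sample size, power, and detectable differences, only group sizes are used: 275/2 is about 137 per group enrolled, and 184/2 = 92 per group before the allowance for losses. Infants lost early contribute part of their time, so the effective number should lie between these.

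**2. Assumptions (none from the documents).** Over 24 weeks in the usual care group, v clinic visits and h hospitalizations or deaths per infant. In the intervention group illness is identical, but care-seeking is lower by a fraction r.

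**3. Composite rate ratio.** RR = [v(1 − r) + h] / (v + h), over v = 0.5, 1, 2 and h = 0.05, 0.1, 0.2:

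| Fall in care-seeking | Range of RR |
|---|---|
| 10% | 0.90 to 0.93 |
| 20% | 0.81 to 0.86 |
| 30% | 0.71 to 0.79 |

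The extremes are (0.5 × 0.9 + 0.2)/0.7 = 0.93 and (2 × 0.7 + 0.05)/2.05 = 0.71. Every value favours the intervention.

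**4. How often this would look significant.** Take h = 0.12, v from 1 to 2, and a between-infant (frailty) variance k = 0.5. With m0 and m1 the mean counts per infant in the two groups and n infants per group,

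SE(log RR) = √[1/(n·m0) + 1/(n·m1) + 2k/n],

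and the chance of a significant result in favour of the intervention at two-sided 5% is Φ(−log RR/SE − 1.96).

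Worked case, v = 1, r = 0.2, n = 137: m0 = 1.12, m1 = 0.8 + 0.12 = 0.92, RR = 0.821, log RR = −0.197. SE = √(0.00652 + 0.00793 + 0.00730) = 0.1475. The ratio is 1.334, and Φ(1.334 − 1.96) = 27%.

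| Fall in care-seeking | n = 92 | n = 137 |
|---|---|---|
| 10% | 8% to 10% | 9% to 13% |
| 20% | 19% to 29% | 27% to 40% |
| 30% | 40% to 59% | 54% to 76% |

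With no difference in care-seeking the figure would be 2.5%. With fewer visits the effect shrinks: at v = 0.5, a 20% fall and n = 137, it is 16%.

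**5. Offsetting.** For RR to return to 1, hospitalizations plus deaths must be multiplied by 1 + v·r/h. For a 20% fall over the grid in step 3, this runs from 1 + 0.5 × 0.2/0.2 = 1.5 to 1 + 2 × 0.2/0.05 = 9. The composite on its own is therefore governed by visits.

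**The case against.** Two stronger readings are tempting, and the documents support neither.

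**That the plan scores a harm it has named as a benefit.** Table 2 and the objectives state a favourable direction only for hospitalization and death. Count outcomes says that counts are compared and the intensity rate reported; it never says that fewer clinic visits are a gain. Nor does Safety events mention withheld care for illness: it speaks of reduced monitoring, as one of several potential consequences, and takes immunization history as the proxy. The step to fewer sick visits is a plausible inference, not the protocol's statement.

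**That a rise in hospitalization or death would be hidden.** Step 5 shows that the composite alone could mask one. But time to first death or hospitalization is analysed without clinic visits, and Table 1 schedules a hospital record review for these events at 24 weeks. The Data Safety Monitoring Board sees secondary endpoints by group at the interim analysis and reviews unblinded safety data. Table 1 also schedules a health questionnaire and anthropometrics at all four follow-up visits, which do not depend on clinic attendance.

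It is also fair to say that the inputs are assumed, that small falls in care-seeking have small effects, that the secondary endpoints are declared unpowered and exploratory, and that reporting by component may be left to an analysis plan not shown here.

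What stands is what the article fixes: an equal-weight composite that differs from Table 2 and adds a component sensitive to care-seeking, reported by unblinded mothers.

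**Conclusion.** The point holds for the mean cumulative function and Poisson analyses in Count outcomes, and only there. Their event set is wider than the endpoint in Table 2, and the added component can fall without any change in illness. Under the assumed rates, a 10% to 30% fall in care-seeking moves the composite rate ratio to about 0.93 to 0.71. The chance of a spurious significant benefit ranges from roughly one in ten at a 10% fall to 40% to 76% at a 30% fall.

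The bias is conditional: reduced monitoring must occur, mainly in the intervention group, and take the form of fewer sick visits. The conclusion on exclusive breastfeeding and the time-to-first analysis do not depend on it. This is an inexpensive improvement to an exploratory analysis, not a threat to the trial's main result.

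**What to change.** - In Count outcomes, use the Table 2 composite, hospitalization and death, for the infant-health count analysis (mean cumulative function and Poisson model). This also reconciles the two definitions.
- Analyse non-routine or sick-clinic visits separately by group, as a care-use outcome with no presumed favourable direction.
- Show those visits in the safety tables beside the immunization proxy, so that reduced monitoring can be judged from both.
- State that fewer visits will not be read as a health gain unless hospitalization and death point the same way.

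Make the change before the study team sees results by group. It needs revised wording and one more table, and no new data, since every item is already collected. The downside is precision: the count analysis loses what is probably its most frequent component and will rest on fewer events.

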### Sample size, power, and detectable differences

We expect an exclusive breastfeeding rate of 8% at age 6 months in the usual care group [17]. We want to detect a difference of 15% between the intervention and usual care groups (i.e., 23% vs 8%). The traditional fixed sample size computations using WinPepi give a sample size of 182 for a two-sided test. Using inflation factor 1.01 for two planned analyses of O’Brien-Fleming boundaries at the 0.05 significance level and 80% power, we compute the maximum sample size of 182 × 1.01 = 184. The sample size is inflated by 33% to 275, to account for loss to follow-up (30%) and infants who test HIV positive (3%) who are included in the analysis ignoring infant HIV status and repeat the analysis excluding HIV-infected infants. The study is not powered for the co-primary endpoint (i.e., any form of breastfeeding rate at 6 months of age) and secondary endpoints. The co-primary and secondary endpoint analyses are considered exploratory and may only be supportive of the primary analysis of exclusive breastfeeding endpoint. No adjustment to the significance level for testing of multiple co-primary endpoints is made since all the co-primary endpoint analyses are considered exploratory.

